## Discussion

3

Although a number of studies have reported on knowledge evaluation among patients with type 1 and gestational DM, literature related to knowledge evaluation among patients with newly diagnosed T2DM is limited, and no studies were located which used a web-based educational intervention to improve the knowledge about newly diagnosed T2DM. For these reasons, this study focused on evaluating patients of newly diagnosed T2DM in rural China, self-management, healthy diet, exercise, and lifestyle habits. Therefore, the primary objective of the present study was to evaluate the efficacy of web-based educational intervention on psychological outcomes and glycemic control in newly diagnosed T2DM in rural China.

Among the limitations of the trial, it should be noted that no blinding was used regarding group allocation, which is difficult in this type of study. Secondly, changes in medication were not taken into account. Medication adjustments in these participants are inevitable, and they may have an influence both on the intervention and control group. Finally, the sample came from a single health center. Therefore, the results cannot be generalized for the entire population.

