### Study population

2.2

Eligibility criteria for the study includes newly diagnosed with T2DM, adult patients (age ≥30 years) regardless of gender; speak and understand Chinese languages; having no significant comorbidity; being not involved in any trial/study related to diabetes during last 3 months and able to attend regular visits. Participants will be excluded if they are of other types of diabetes (gestational diabetes, T1DM); unable to answer the questionnaire independently or having hearing, vision, or cognitive impairments.

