### Intervention and control protocols

2.4

Patients in the intervention group attended the standard clinic-based education and additionally used the web-based education intervention. Access to the web-based education intervention (A touch screen computer) took place at the diabetes clinic at our hospital, supervised by the researcher. The program provided information on healthy diet and healthy lifestyle and included pictures and simple instructions. The program took 15 to 30 minutes to complete. Patients were also given the URL link for the website, so they could access the website as they wished at home.

Patients in the control group attended the standard clinic-based education class alone. The single, group education class, lasting 1.5 hours, is run by Health's dieticians and diabetes educator nurses. Generally 5 to 8 newly diagnosed T2DM patients attend. Session and content is based on healthy diet, exercise, healthy lifestyle, and blood glucose level monitoring.

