### Outcomes

2.5

Questions on the patients’ sociodemographic characteristics concerned their age, sex, marital status, level of education, and occupation type (Table 1). Fasting blood glucose level was measured in mmol/L from a venous blood sample. Health-related quality of life was measured by the EQ-5D-3L questionnaire, which is a validated generic instrument used in clinical settings for general population and for economic evaluation. Based on the real-time information, we would also assess the patient conditions and offer corresponding suggestions for better self-management. The Self-rating Anxiety Scale and Self-rating Depression Scale are the scales for assessing anxiety and depression, which includes 20 problems respectively, using a 4-point scale ranging from 1 (none, or a little of the time) to 4 (most, or all of the time). The statistical score of all questions were calculated after completion of the answers (Table 2).

**Table 1 T1:** Patient baseline demographics.

Demographics	Education group	Control group	*P* value
Number of patients			
Age^†^ (years)			
Male sex (no. [%])			
BMI^†^ (kg/m^2^)			
Follow-up^†^			

BMI = body mass index.

† The values are given as the mean and the SD.

**Table 2 T2:** Postoperative outcomes.

Outcomes	Education group	Control group	*P* value
Fasting blood glucose level^†^			
EQ-5D-3L questionnaire^†^			
Self-rating Anxiety Scale^†^			
Self-rating Depression Scale^†^			

† The values are given as the mean and the SD.

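### Difficulty explains not blinding patients and educators, but not leaving questionnaire collection, scoring, sample handling and analysis unmasked

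*Protocol article*

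**What the plan says.** The Discussion of the protocol article names the absence of blinding first among the limitations: "no blinding was used regarding group allocation, which is difficult in this type of study". No role is distinguished, and difficulty is the only reason given.

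Section 2.5 (Outcomes) describes four outcomes:

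- Glucose: "Fasting blood glucose level was measured in mmol/L from a venous blood sample".
- Quality of life: "Health-related quality of life was measured by the EQ-5D-3L questionnaire".
- Mood, with two instruments of 20 items each: "The Self-rating Anxiety Scale and Self-rating Depression Scale are the scales for assessing anxiety and depression". The patient answers "using a 4-point scale ranging from 1 (none, or a little of the time) to 4 (most, or all of the time").

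On contact with study staff, section 2.4 says of the education arm: "Access to the web-based education intervention (A touch screen computer) took place at the diabetes clinic at our hospital, supervised by the researcher". Both arms attend the standard class given by dieticians and diabetes nurses; the web program is added in the education arm only. Section 2.2 excludes patients who are "unable to answer the questionnaire independently or having hearing, vision, or cognitive impairments". Section 2.6 lets a Kolmogorov–Smirnov check decide between the t test and the Mann–Whitney test.

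The article does not say who hands out, collects or scores the questionnaires, who runs the assay or who analyses the data.

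**The concern.** Blinding is not one decision but several, one for each role. A reason that holds for one role need not hold for another. The article gives one reason and applies it without limit, so roles that could readily be masked are covered by an argument that does not fit them.

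The psychological half of the primary objective rests wholly on self-ratings, with no objective measure behind it. If the person who supervises the web sessions is also present when patients fill in the scales, education-arm patients may give more favourable answers out of courtesy, and control patients would not have the same relationship. Staff who know the arm can also influence how incomplete forms are chased and how scores are entered. An analyst who knows the arm makes the choice of test with the direction of the result in view. That choice follows a look at the data, and none of the four outcomes is named as the single primary one, which leaves more room for such influence.

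**Working it through.** The article states no figure on this point, so there is nothing to reproduce. The check has three steps.

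**1. Outcomes by who rates them (section 2.5)**

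| Outcome | Source | Self-rated? |
|---|---|---|
| Fasting glucose | Laboratory, venous sample | No |
| EQ-5D-3L | Patient | Yes |
| Self-rating Anxiety Scale | Patient | Yes |
| Self-rating Depression Scale | Patient | Yes |

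Three of four outcomes are self-ratings.

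**2. Does the stated reason fit each role?**

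| Role | Must know the arm? | Does difficulty explain no masking? |
|---|---|---|
| Patient | Yes, web use is visible | Yes |
| Researcher or nurse giving or supervising education | Yes | Yes |
| Person handing out and collecting forms | No | No |
| Person scoring forms | No | No |
| Person handling samples, laboratory | No | No |
| Analyst | No, arms can be coded | No |

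The reason holds for two of the six roles and fails for four.

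**3. How sensitive is a self-rated outcome to a response shift?**

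This step is an illustration. The inputs are:

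- alpha 0.05 (section 2.6), taken as two-sided because the article does not say;
- n per arm, assumed, with equal arms;
- response shift b in SD units in one arm, assumed;
- true effect zero.

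The probability of P < 0.05 in a two-sample z test is

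1 − Φ(1.96 − b/√(2/n)) + Φ(−1.96 − b/√(2/n)).

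For n = 100, 1/√(2/n) = √50 = 7.07.

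- b = 0.2: 0.2 × 7.07 = 1.41, and P(Z > 1.96 − 1.41) is about 0.29.
- b = 0.3: 0.3 × 7.07 = 2.12, and P(Z > 1.96 − 2.12) is about 0.56.

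Nearly all of these rejections lie in the direction of the shift. Without bias, 2.5% would fall on that side. The wider grid, counting rejections in both directions, is:

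| Shift (SD) | n = 30 | n = 50 | n = 100 | n = 200 |
|---|---|---|---|---|
| 0 | 5.0% | 5.0% | 5.0% | 5.0% |
| 0.1 | 6.7% | 7.9% | 10.9% | 17.0% |
| 0.2 | 12.1% | 17.0% | 29.3% | 51.6% |
| 0.3 | 21.3% | 32.3% | 56.4% | 85.1% |

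The false-positive rate rises with sample size, so recruiting more patients does not cure it. The shift b is the whole response bias: the patient's own expectancy plus any effect of who is present. The article gives nothing from which to split the two.

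**The case against.** Four arguments on the other side deserve weight.

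- **The patient is the assessor.** Coded forms, masked scoring and a coded analysis all leave the patient knowing the arm. This stands. A reader might infer that response bias could be removed at little cost; the article does not support that. Removing it would need a control program that masks patients, which is a different design.
- **The researcher's presence at completion is not documented.** Section 2.4 places the researcher at the web sessions, not at the questionnaires, and section 2.2 suggests patients answer for themselves. Section 2.5 also has the study team reviewing patients and advising them on self-management, without limiting this to one arm. This stands too. A reader might infer that the ratings are biased in the education arm only, but that is an open risk and not an established fact.
- **Logistics are often left to a full protocol.** True of labels and forms, and their absence alone would be no finding. Here, however, the article states positively that no blinding was used and gives a reason. The point concerns the reach of that reason.
- **The maskable steps matter least.** Glucose is a laboratory value and fixed-item scales leave a scorer little discretion. This is largely right for scoring and assay. It is less so for who attends completion and for an analysis in which the test is chosen after seeing the data.

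The protocol also deserves credit for disclosing the limitation openly; nothing is hidden or contradictory.

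**Conclusion.** The point holds in a limited form. The stated difficulty justifies not blinding patients and educators. It does not justify leaving questionnaire collection, scoring, sample handling and analysis unmasked when three of four outcomes are self-ratings and the researcher supervises the education arm's web sessions.

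Masking these steps would lower bias from staff presence, handling and analysis. It would not remove expectancy bias, and the size of the gain cannot be computed from the article. The 29% to 56% figures should not be read as the price of leaving the steps unmasked: they size total response bias on one scale, and they rest on an assumed 100 patients per arm and an assumed shift of 0.2 to 0.3 SD. With 50 per arm and 0.1 SD the figure is 7.9%. They show only that a modest shift is enough to matter.

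**What to change.** - **Section 2.5, questionnaires:** state that the EQ-5D-3L and both self-rating scales are completed by the patient alone, before any educational contact at the visit, and without the supervising researcher or education nurses present. Forms can be handed to existing reception or laboratory staff. The exclusion in section 2.2 makes unattended completion feasible.
- **Section 2.5, handling:** identify forms and blood samples by study number only, and score the forms without knowledge of arm.
- **Section 2.6:** run the main analysis, including the choice between the t test and the Mann–Whitney test, on arms coded A and B. The code should be held by someone outside the analysis.
- **Discussion:** limit the statement on blinding to patients and educators, and add that response bias from patients knowing their arm remains on the three self-rated outcomes and must be weighed in interpretation.

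The cost is protocol wording and a small change of visit workflow with existing staff. The downside is a few more missing items, because nobody checks the form with the patient. Section 2.6 speaks of the analyses in the future tense, so a masked analysis should remain possible even if visits have begun.
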